## Continuous Efficacy Endpoints

For continuous efficacy endpoints, missing observations will not be formally imputed. Mixed Model for Repeated Measures (MMRM) analysis will be used with all available data, including participants with partial data (i.e., with missing data) in order to arrive at an estimate of the mean treatment effect. MMRM is based on the assumption of missing at random (MAR), i.e., dropout would behave similarly to other participants in the same treatment group and possibly with similar covariate values, had they not dropped out.

Unless otherwise indicated, in other cases the observed data will be used and no imputation will be performed.

## Scoring Derivations

Several instruments will be used in this study to measure some underlying construct. As such, missing data in this type of instruments can occur on the item scores. Missing data will be handled as described by the author of each instrument and detailed in the relevant endpoint section, or, if no information is stated by the author, no imputation will be done and such scores (and any resultant domain/total score) will remain missing.

### 7.3.2 Handling of Missing or Incomplete Dates

Imputation rules for missing or partial AE start date are defined below:

**If only Day of AE start date is missing:**

If the AE start year and month are the same as that for the first dose date, then:

- If the full (or partial) AE end date is NOT before the first dose date or AE end date is missing, then impute the AE start day as the day of first dose date; otherwise, impute the AE start day as 1.

If the AE start year and month are not same as that for the first dose date, then, impute the AE start day as 1.

Compare the imputed AE start date with treatment-emergent (TE) period to determine whether the AE is pre-treatment AE, treatment-emergent adverse event (TEAE) or post-treatment AE.

**If Day and Month of AE start date are missing:**

If AE start year = first dose year, then:

- If the full (or partial) AE end date is NOT before the first dose date or AE end date is missing, then impute the AE start Month and Day as the Month and Day of first dose date; otherwise, impute the AE start Month as January and the Day as 1.

If AE start year not same as first dose year, then, impute the AE start MONTH as January and the DAY as 1.

Compare the imputed AE start date with TE period to determine whether the AE is pre-treatment AE, TEAE or post-treatment AE.

**If Year of AE start date is missing:**

If the year of AE start date is missing or AE start date is completely missing, then query site with no imputation. Also compare the full (or partial) AE end date to the first dose date. If the AE end date is before the first dose date, then the AE should be considered as a pre-treatment AE. Otherwise, the AE will be considered as TEAE.

Imputation rules for missing or partial medication start/stop dates are defined below:

**Missing or partial medication start date:**

- If only DAY is missing, use the first day of the month.
- If DAY and Month are both missing, use the first day of the year.
- If DAY, Month and Year are all missing, use a date before the first dose date.

**Missing or partial medication stop date:**

- If only DAY is missing, use the last day of the month.
- If DAY and Month are both missing, use the last day of the year.
- If DAY, Month and year are all missing, then consider the medication is still 'continuing' and date will not be imputed.

Imputation rules for missing or partial PsA start dates are defined below:

**Missing or partial PsA start date:**

- If only DAY is missing, use the first day of the month.
- If DAY and Month are both missing, use the first day of the year.
- If DAY, Month and Year are all missing, use a date before the first dose date.

**7.3.3 Randomization Stratification Errors**

Randomization stratification errors can occur if the incorrect Sex or Prior Biologic Use is entered in the IRT system at the time of randomization. The FAS analyses will follow the ITT principle and analyse these participants according to the randomized stratum.

## 8 STATISTICAL METHODS

### 8.1 General Statistical Conventions

All statistical procedures will be completed using SAS version 9.4® or higher.

For continuous variables, descriptive statistics (number of observations, mean, standard deviation (SD), minimum (min), first quartile, median, third quartile and maximum (max) and 95% confidence intervals (CIs) as appropriate) will be presented. Summaries of hs-CRP and PK concentration will include the geometric mean (GM) and coefficient of variation (CV). The count of missing observations will be provided in all descriptive tables.

Categorical variables will be presented as counts and percentages with non-missing values in each category. The number of missing values will be presented as a separate category, if there is at least one missing value. Unless otherwise stated, all statistical testing will be two-sided and will be performed using a significance (alpha) level of 0.05. For all statistical analyses, p-values and 95% CIs will be provided. All sensitivity analyses will be regarded as exploratory and as such no formal adjustment for multiplicity will be made.

Number of decimal places will be presented as follow:

- continuous variables: for min and max, the decimals will be used as captured in the database; arithmetic mean, median and quartiles will be depicted with one more decimal than captured in the database; and SD will be depicted with two more decimals than captured in the database.
- categorical variables: percentages will be rounded to one decimal place and a percentage of 100% will be reported as 100%.
- the p-values will be rounded and displayed to 3 decimal places, values less than 0.001 will be displayed as 'p<0.001' and values higher than 0.999 will be displayed as 'p>0.999'.

This study has two parts Part A and Part B:

**Part A Analysis:** For Part A, summaries and analyses will be based on the data collected from the visits Week 0 to Week 12. Unless otherwise stated, the summary statistics and analyses will be presented for the following treatment groups:

- Sonelokimab 120 mg Q2W;
- Sonelokimab 60 mg Q2W;
- Sonelokimab 60 mg Q4W;
- Placebo;
- Adalimumab.
- Total sonelokimab (safety tables only)

**Part B:** For Part B no statistical testing will be performed. Summary statistics will be based on the data collected from the visits Week 12 to Week 24.

Unless otherwise stated, the summary statistics will be presented for the following treatment groups:

- Sonelokimab 120 mg Q2W→sonelokimab 120 mg Q4W;
- Sonelokimab 120 mg Q2W→adalimumab 40 mg Q2W;
- Sonelokimab 60 mg Q2W→sonelokimab 60 mg Q4W;
- Sonelokimab 60 mg Q2W→sonelokimab 120 mg Q4W;
- Sonelokimab 60 mg Q4W→sonelokimab 60 mg Q4W;
- Sonelokimab 60 mg Q4W→sonelokimab 120 mg Q4W;
- Placebo→sonelokimab 120 mg Q4W;
- Adalimumab 40 mg Q2W→adalimumab 40 mg Q2W;
- Adalimumab 40 mg Q2W→sonelokimab 120 mg Q2W.
- Total sonelokimab (safety tables only)

**Part A+B:** For Part A+B no statistical testing will be performed. Summary statistics will be based on the data collected from the visit Week 0 to Week 24. Part A+B tables will only be presented for adverse events.

Unless otherwise stated, the summary statistics will be presented for the following treatment groups:

- Placebo (Part A only)
- Total Sonelokimab 120mg
- Total Sonelokimab 60mg
- Total Adalimumab 40mg Q2W
- Total Sonelokimab

For the total groups they will have different subjects potentially for Part A and Part B and subjects will only have results shown for the Part when they took the relevant treatment.

All participant data, including those derived, will be presented in individual participant data listings. Unless otherwise stated, unscheduled visit results will be included in date/time chronological order, within participant listings only. All listings will be sorted by treatment group, investigational site, participant number, date/time, and visit. The treatment group as well as participant's sex, age and race will be stated on each listing. Unless otherwise stated, safety data listings will be based on SAF and efficacy data listings will be based on FAS.

## 8.2 Participant Disposition

The number and percentage of participants screened, randomized, randomized and treated, randomized and not treated and the number of participants in each of the analysis sets (including reasons for exclusion) separately for Part A and Part A+B (see [section 7](#)) will be summarized by treatment group on the enrolled set.

The number and percentage of participants will also be summarized for the following participant disposition categories:

- Completed Part A, defined as completing a visit in the Week 12 visit window or a later visit
- Completed study drug for Part A, defined as received the Week 10 dose or a dose at a later visit
- Discontinued study drug in Part A
- Received study drug in Part B, defined as received a dose at Week 12 or a later visit
- Completed study drug treatment for both part A and part B per-protocol;
- Discontinued study drug earlier during Part B (including the primary reason for discontinuation);
- Completed the study at week 24;
- Completed the study including post-treatment follow-up;
- Discontinued from study early (including the reason for discontinuation).

Given data from Part A and Part B will be combined together (including participants not entering Part B), all distinct treatment groups detailed in section 9.1 from Part A and B will be presented.

The time in days to study drug discontinuation due to any reason will be displayed with plot by initial randomized treatment for the FAS during Part A. The time to last visit will be defined as the discontinuation date minus the first dose date plus one.

The plot will be repeated for Part A+B to show the time to discontinuation of sonelokimab. This will only include subjects exposed to sonelokimab in either Part A or B. The time to discontinuation will be defined as the discontinuation date minus the first sonelokimab dose date plus one. Subjects who complete the treatment at Week 24 will be censored at the completion day (Week 24).

A listing of participant disposition will be provided for enrolled set.

A listing of analysis set and reasons for exclusion from the analysis set will be provided for enrolled set.

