### **8.3.5 Safety Follow-up Visit**

Participants are to attend a Safety Follow-up Visit 8 weeks ( $\pm 7$  days) after the administration of the last dose of study treatment.

If the participant no longer wants to take part in the study (i.e., they prematurely discontinue the study and/or withdraw consent), they will attend the EOT Visit as described in the SOA in Section [3](#), [Table 1](#), and be discontinued from the study. Every reasonable effort will be made to have discontinued participants attend the Safety Follow-up Visit.

Note this exception to scheduling the Safety Follow-up Visit: Participants who decide to discontinue the treatment in Part A should continue to attend all future scheduled visits through Week 12 for safety and efficacy assessments (as described in Section [9.4](#)). A separate Safety Follow-up Visit is not required in this case if the participant attends a scheduled visit at 8 weeks after treatment discontinuation.

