## 3 STUDY DESIGN

### 3.1 General Study Design

This is a phase 2, multi-center, randomized, parallel-group, double-blind, placebo-controlled study evaluating the efficacy, safety, PK and IG of sonelokimab in participants with active PsA. This study also has an active reference arm of adalimumab treatment; however, no formal comparison of sonelokimab vs adalimumab is planned.

For US participants, the study includes a screening period of up to 28 days, a 12-week treatment period (Part A) and an 8-week safety follow-up period after the administration of the last dose, which is scheduled to be administered at Week 10. An end of treatment (EOT) visit will be performed at Week 12. A safety follow-up visit will be performed 8 weeks ( $\pm 7$  days) after the administration of the last dose of study treatment. For non-US participants, the study will include screening period of up to 28 days, a treatment period of up to 24 weeks, and a safety follow-up period of 8 weeks after the last dose of study treatment. The treatment period will be divided into 2 parts: Part A (from baseline to Week 12) and Part B (from Week 12 to Week 24). The overall treatment period (Part A+B) will be from baseline to Week 24. The overall treatment period (Part A+B) will be from baseline to Week 24. The final dose of study treatment is scheduled to occur at Week 22. An End of Treatment (EOT) visit will be performed at Week 24. A safety follow-up visit will be performed 8 weeks ( $\pm 7$  days) after the administration of the final dose of study treatment.

On the first day of the Part A (Day 1/Week 0), eligible participants will be randomized 1:1:1:1:1 to one of 5 treatment arms as described in [Figure 1](#).

Randomization will be stratified by sex (Male/Female) and exposure to biologic agents prior to the Screening Visit (Yes/No). The total number of participants with previous use of biologic agents will be capped at 30%.

Dosing in the sonelokimab arms will continue through Week 8. Adalimumab will be given through Week 10. All treatment arms will receive placebo as required to maintain the blinding of the study. The Part A treatment period will end at Week 12 when the primary efficacy analysis will be performed, comparing each of the sonelokimab treatment arms (sonelokimab 120 mg Q2W, sonelokimab 60 mg Q2W, sonelokimab 60 mg Q4W) vs placebo.

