**Table 1: Treatment Allocation in Part A+B**

| Treatment Assignment in Part A | Treatment Allocation in Part B (Based Upon Response at Week 12) |                        |
|--------------------------------|-----------------------------------------------------------------|------------------------|
|                                | Responder                                                       | Non-responder          |
| Arm 1: Sonelokimab 120 mg Q2W  | Sonelokimab 120 mg Q4W                                          | Adalimumab 40 mg Q2W   |
| Arm 2: Sonelokimab 60 mg Q2W   | Sonelokimab 60 mg Q4W                                           | Sonelokimab 120 mg Q4W |
| Arm 3: Sonelokimab 60 mg Q4W   | Sonelokimab 60 mg Q4W                                           | Sonelokimab 120 mg Q4W |
| Arm 4: Placebo                 | Sonelokimab 120 mg Q4W                                          | Sonelokimab 120 mg Q4W |
| Arm 5: Adalimumab 40 mg Q2W    | Adalimumab 40 mg Q2W                                            | Sonelokimab 120 mg Q2W |

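### SAP 8.2 lets a Safety Follow-up visit count as completing Part A, and its sonelokimab discontinuation plot has no censoring rule for planned Week 12 completion or planned switching

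*Combined protocol and SAP*

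**What the plan says.** **Completion row.** SAP 8.2 defines the category as "Completed Part A, defined as completing a visit in the Week 12 visit window or a later visit". It does not name any visit type that fails to count, does not require the participant to be still in the study, and does not say which of the Week 12 windows in SAP 7.2 applies.

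**Visits after withdrawal.** Protocol 9.4 asks participants who stop drug in Part A to keep attending through Week 12, and withdraws from the study those who do not agree. Protocol 8.3.5 places Safety Follow-up 8 weeks (±7 days) after the last dose and adds: "Every reasonable effort will be made to have discontinued participants attend the Safety Follow-up Visit".

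**Sonelokimab plot.** For the Part A+B plot, SAP 8.2 sets the population ("This will only include subjects exposed to sonelokimab in either Part A or B") and the time variable ("The time to discontinuation will be defined as the discontinuation date minus the first sonelokimab dose date plus one"). The only censoring statement is "Subjects who complete the treatment at Week 24 will be censored at the completion day (Week 24".

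**Who cannot reach Week 24 on sonelokimab by design.** SAP 3.1 states: "For US participants, the study includes a screening period of up to 28 days, a 12-week treatment period (Part A", and, for the same participants, "An end of treatment (EOT) visit will be performed at Week 12". In SAP Table 1, the row "Arm 1: Sonelokimab 120 mg Q2W" allocates non-responders to adalimumab for Part B.

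**The concern.** The completion row is meant to show how many participants in each arm reached the Week 12 assessment. As worded, it can be met by a safety visit made after the participant has left the study. Under SAP 7.3.1 the same person is a non-responder by imputation at Week 12, so the disposition table and the efficacy data would describe that person differently.

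The plot is meant to show persistence on sonelokimab. Two groups stop sonelokimab at Week 12 because the design says so: US participants, and Arm 1 non-responders who enter Part B. The single censoring rule does not cover the first group. On its literal wording it treats the second as followed on sonelokimab to Week 24. Two programmers working from this text could draw different curves.

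**Working it through.** **1. Reproduce the plan's own figures.** SAP 7.2 builds windows by bisecting adjacent planned days and rounding down. For the ACR components (planned Days 57, 85 and 99 around Week 12):
- lower limit = floor((57 + 85)/2) + 1 = 71 + 1 = 72;
- upper limit = floor((85 + 99)/2) = 92.

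This matches the stated Day 72–92. The nominal Safety Follow-up for a full course is 155 + 56 = Day 211, as stated. The US study duration is 4 + 10 + 8 = 22 weeks, as stated.

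**2. Safety Follow-up day for an early withdrawal** = last-dose day + 56, ±7. Dose days come from the Schedule of Activities. The last two columns ask whether that visit falls in the Week 12 window or later, under two of the SAP's windows.

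| Last dose | Dose day | Follow-up day (range) | ACR-component window (from Day 72) | Vital-signs window (from Day 79) |
|---|---|---|---|---|
| Week 0 | 1 | 57 (50–64) | never | never |
| Week 2 | 15 | 71 (64–78) | only on Days 72–78 | never |
| Week 4 | 29 | 85 (78–92) | always | from Day 79 |
| Week 6 | 43 | 99 (92–106) | always | always |
| Week 8 | 57 | 113 (106–120) | always | always |
| Week 10 | 71 | 127 (120–134) | always | always |

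Other Week 12 windows in SAP 7.2 are Day 72–99 (PASI, safety laboratory), 58–99 (urinalysis, SF-36v2), 2–127 (BSA, mNAPSI) and 2–148 (ECG). Under the ECG window every row of the table would qualify. The answer for Weeks 0 and 2 therefore depends on a choice that 8.2 does not make. For last doses at Weeks 6, 8 and 10 the visit qualifies under all of them, and for Week 4 under all except a Day 78 visit judged by the vital-signs window.

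**3. No efficacy data at that visit.** The Schedule of Activities has no joint counts, PtGADA, PtAAP, HAQ-DI, PhGADA or hs-CRP at Safety Follow-up. A participant seen only there has no Week 12 ACR assessment.

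**4. Direction.** Everyone who attends the Week 12 visit meets the 8.2 definition. The definition can only add people to that group, so the completion rate can be overstated but not understated.

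**5. The plot, US participants.** Their Week 12 EOT visit is at Day 85 and their Safety Follow-up is at about Day 71 + 56 = 127. None can complete treatment at Week 24 (Day 169), so none meets the censoring rule, and 8.2 gives no other. SAP 8.6.2.1 and 8.6.2.9 do recognise Week 12 completion by US participants, for LOCF; 8.2 has no counterpart.

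**6. The plot, Arm 1 non-responders.** First sonelokimab dose is Day 1 and Part B allocation is at Day 85. One who finishes Part B on adalimumab completes treatment at Week 24 and, on the literal wording, is censored at 169 − 1 + 1 = 169 days. Time to allocation is 85 − 1 + 1 = 85 days. The difference is 84 days, or 12 weeks, during which the participant was assigned adalimumab.

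**The case against.** **These are descriptive displays.** This stands. A reader might infer that the completion row props up the primary result. The documents do not support that: non-responder imputation in SAP 7.3.1 is driven by study discontinuation, missing data and prohibited medication, and never refers to the completion row. An observed-data analysis is also planned.

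**Early withdrawals remain visible elsewhere.** Partly right. The table also reports completion and discontinuation of study drug in Part A, and early discontinuation from the study with reasons. However, the drug rows include people who properly stayed for their Week 12 visit, and the study row is not split by part. No row isolates study withdrawal before Week 12.

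**Most people who stop drug in Part A are genuine completers.** This stands for those who keep attending through Week 12 under protocol 9.4. It would be wrong to read the table above as saying that four of six last-dose visits produce false completion. It counts dose visits, not participants, and applies only to those withdrawn from the study who return for Safety Follow-up alone.

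**The later-visit wording has an innocent purpose.** Protocol 8.6 moves the response assessment to Week 14 when Week 12 is missed, and SAP 7.2 treats Safety Follow-up as its own nominal visit in several windows. That may well be the intention, but 8.2 does not say it.

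**US participants are not declared to be events.** This stands. A reader might infer that they would be plotted as discontinuations, with a false drop of 10 to 30 percentage points if 10% to 30% of about 120 sonelokimab-randomised participants were in the US. The documents support neither step. The SAP leaves these participants without a rule, and elsewhere calls them completers. It gives no US share. The plot population also includes placebo participants and adalimumab non-responders who start sonelokimab in Part B, so 120 is not the denominator.

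**For Arm 1, completing treatment could mean completing sonelokimab.** A possible reading, but then these participants too have no stated rule. Either way the text needs a sentence.

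**Conclusion.** The point holds as a defect in two descriptive displays. On its stated wording, the completion row admits participants withdrawn from the study in Part A who return only for Safety Follow-up after a last dose at Week 4 or later, and some after Week 2. The resulting error is upward only. The sonelokimab plot states no rule for US participants who complete at Week 12, and its literal rule follows Arm 1 non-responders for 12 weeks beyond their planned move off sonelokimab.

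The primary and key secondary analyses and the sample size are unaffected. No size can be given: the documents report neither the US share nor how many withdrawals would be seen only at Safety Follow-up. The conclusion on the completion row assumes that some withdrawn participants do return for that visit, which the protocol asks sites to pursue.

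**What to change.** In SAP 8.2:

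- Define completion of Part A as attending the scheduled Week 12 visit, or the Week 14 visit that replaces it under protocol 8.6. Exclude Safety Follow-up visits and EOT visits brought forward by discontinuation. State that the scheduled Week 12 EOT visit of US participants does count.
- Name the Week 12 window used for this row.
- Add a row for withdrawal from the study during Part A.
- In the Part A+B sonelokimab plot, censor US participants who complete treatment at their planned Week 12 end of treatment, and Arm 1 non-responders at the Part B allocation date. Count as events only stops before the planned end or switch.

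The cost is a few sentences, minor reprogramming of one table and one figure, and possibly a slightly lower reported Part A completion rate. No data collection changes.
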